# Feasibility of a custom-tailored, evidence-based, theory-informed, intervention to prevent burnout and reduce stress for healthcare professionals: protocol for a single-arm trial

**DOI:** 10.1186/s40814-024-01553-w

**Published:** 2024-11-07

**Keywords:** Burnout, Prevention, Healthcare professionals, Study protocol, Feasibility, Mind–body medicine

## Abstract

**Background:**

Healthcare professionals face high levels of occupational stress, time pressure, workload, and poor organizational support. This makes them particularly vulnerable to burnout. The COVID-19 pandemic has further exacerbated this situation. This single-arm, multicenter, mixed-methods feasibility study pilots the *LAGOM* program: A tailored, evidence-based intervention to prevent burnout and reduce stress among healthcare professionals.

**Methods:**

Participants will include healthcare professionals (*N* = 30) working at Charité–Universitätsmedizin Berlin and Immanuel Hospital, Berlin. *LAGOM* focuses on support for individual behavior change and personal resources and also addresses the organizational level. The intervention´s feasibility will be evaluated through a non-randomized feasibility trial with a mixed methods process evaluation. The exploratory primary study aims are to assess the acceptability and feasibility of the (1) evaluation procedures and of the (2) intervention content and structure using study records, standardized questionnaires, protocol checklists, and diaries. Exploratory effectiveness analysis will take place as well. Further, semi-structured interviews (*n* = 3 to 6) and electrophysiological measurements (*n* = 20) will be conducted.

**Discussion:**

Custom-tailored, well-implemented multi-level interventions are needed to prevent burnout and reduce stress among healthcare professionals. Long-term strategies are warranted to sustainably implement effective programs. This feasibility study helps to refine trial procedures and content of the *LAGOM* program for a randomized controlled trial to evaluate the intervention’s effectiveness.

**Trial registration:**

German Clinical Trials Register: DRKS00032014, registered 17^th^ October 2023.

**Supplementary Information:**

The online version contains supplementary material available at 10.1186/s40814-024-01553-w.

## Background

Burnout in healthcare professionals is a global problem with both negative health consequences for the individual and negative effects on patient safety, patient care, professionalism, workplace injuries, and absenteeism [1, 2]. The COVID-19 pandemic has exacerbated the situation [3, 4]. Effective interventions to prevent burnout in healthcare professionals are more urgent than ever. Due to the unique and dynamic work environment where healthcare professionals face high levels of occupational stress, time pressure, workload, and, more often than not, poor organizational support [5], the implementation of effective interventions in this context is particularly challenging.

Burnout is a multidimensional construct, often defined by the symptom triad of (1) emotional exhaustion, (2) depersonalization, and (3) reduced personal accomplishment [6]. As individual factors, as well as factors of the working context, play a role in the development of burnout, interventions to address burnout should incorporate both aspects [6]. Both individually oriented and structural strategies have the potential to lead to a clinically significant reduction in burnout among physicians and nurses [7, 8], at best combining both approaches to be as successful as possible [9]. Yet most interventions focus on either one or the other: Either person-directed courses offering a combination of mindfulness, self-care, yoga, massage, meditation, or stress management skills or organization-directed interventions like workload or schedule rotations [8]. Very few interventions combine both approaches [10, 11]. Another significant pitfall of ineffective interventions is the lack of explicitly tailoring the interventions to the specific needs of healthcare professionals and their organizations [12]. This can lead to unintended side effects or low participation, subsequently resulting in no improvements in health outcomes [12]. In addition, assessments of intervention adherence are scarce [12]. This limits the ability to assess whether the intervention was not properly implemented or was simply ineffective [7, 12, 13].

This paper describes the protocol for the *LAGOM* feasibility study. *LAGOM* is a Swedish word describing the “golden ratio”, if something is just right, not too much and not too little, the ideal equilibrium. It is also an acronym for “LAngfristig Gesundheitsbezogene Organisationskonzepte mit Mind–Body Medizin” (Longterm Approach and Guidelines for Occupational Mental health with Mind–Body Medicine). It is a custom-tailored, evidence-based, theory-informed intervention to prevent burnout and reduce stress for healthcare professionals. *LAGOM's* long-term goal is to create a sustainable, health-promoting, and meaningful work environment in hospitals so that work is enjoyable, employees experience job satisfaction, and remain healthy in the long term. The intervention was developed in close collaboration with healthcare professionals throughout the process following the Intervention Mapping Approach (IMA) [14]. *LAGOM* focuses on both individual and structural prevention, precisely addressing the known weaknesses of existing burnout prevention interventions for healthcare professionals [7, 13]. Individualized prevention contains elements of mind–body medicine (MBM), a health practice that combines mental focus, breathing exercises, and body movements to calm down body and mind and promote health and well-being [15]. It encompasses a wide variety of techniques such as meditation, yoga, or guided imagery, and research has proven that there are beneficial effects on multiple physical and mental health conditions related to stress [16, 17]. Due to the complex processes and costs associated with implementing and evaluating such sophisticated behavior change interventions for health professionals, piloting the intervention prior to a confirmatory randomized controlled trial (RCT) is essential.

This feasibility study has two main objectives:Assess the feasibility and acceptability of trial and evaluation procedures (e.g. recruitment rates).Assess the feasibility and acceptability of the *LAGOM* content and structure (e.g. satisfaction with the *LAGOM program*).

## Methods

### Study setting and design

The single-arm, multi-center, mixed-methods feasibility trial will be conducted and reported according to the SPIRIT guideline [18], supplemented by the CONSORT extension to pilot and feasibility trials [19], the Mixed-Methods Article Reporting Standards [20] and the IMA [14]. It received favorable ethical approval from the Ethics Committee of the Charité–Universitätsmedizin Berlin on 14th July, 2023 (EA1/157/23) and has been registered in the German Clinical Trials Register prior to conducting the study (DRKS00032014). The research will adhere to standards of good clinical practice and the declaration of Helsinki. Study sites are the Charité–Universitätsmedizin, Berlin and the Immanuel Hospital, Wannsee, Germany. A mixed methods sequential explanatory design will be used which consists of two phases, a quantitative phase, followed by a qualitative phase [21] as depicted in Fig. 1. First, quantitative data is collected and analyzed. In the second step, qualitative data is collected and analyzed to follow up on the experiences of participants and elaborate on the quantitative results. The qualitative phase builds upon the quantitative phase and the two phases are connected at the intermediate stage of the study as well as at the interpretation stage. This mixed-methods approach enables the quantitative data and analysis to provide a general understanding of the feasibility of the intervention. Subsequently, the qualitative data and analysis will follow up on the experiences of participants with the intervention by exploring participants´ views in more depth and help refine and explain quantitative data [22].

**Fig. 1 Fig1:**
[figure not shown]
Mixed methods sequential explanatory design flowchart, adapted from Ivankowa, Creswell & Stick, 2006, p. 16 [23]

### Eligibility criteria

Healthcare professionals working at Charité–Universitätsmedizin Berlin or Immanuel Hospital, Wannsee, Germany will be invited to participate. Table 1 outlines the inclusion and exclusion criteria.

**Table 1 Tab1:** Eligibility criteria

Inclusion criteria
• Working Healthcare professionals, actively practicing medicine or nursing at Charité–Universitätsmedizin Berlin or Immanuel Hospital, Wannsee, Germany • 18 years or older • Completed written informed consent • Proficient in the German language
Exclusion criteria
• Clinically diagnosis of burnout syndrome according to ICD-11 (QD85 “Burnout”) • Pregnancy • Solely administrative position

### Recruitment procedure

Participants for the *LAGOM* program will be recruited by the research team via the hospitals´ intranet, notices, and informational events, as well as by word of mouth at Charité–Universitätsmedizin Berlin and Immanuel Hospital. The management supports the participation of their employees by scheduling time off for course hours. Eligible participants will be informed about the study process and will receive written study information to take home and read at their convenience. A few days later, they will be contacted via telephone by a member of the study team and asked if they would like to participate. During telephone contact, participants will be given the opportunity to ask questions to clarify any uncertainties. Interested participants will then provide written informed consent and complete the baseline questionnaire to be enrolled in the study. Reasons for not granting consent or completing the baseline survey will be recorded. All participants will be explicitly informed that they can withdraw from the study at any time without giving reasons and that this will not have any negative consequences for their jobs.

### Intervention

#### Intervention development

The intervention development followed the IMA by Eldredge et al. (2006) [14]. In addition to the project team, which consists of physicians, psychologists, nutritionists, sports scientists, and physical medicine specialists, various advisory boards were involved in intervention development. A group of stakeholders, consisting of physicians and nurses, the target group of the intervention, also formed part of the expert advisory boards. This stakeholder expert advisory board gave continuous feedback during the intervention development phase and this assessment informed and tailored the program specifically to ensure that the needs of the target group will be addressed. The *LAGOM* program and the IMA steps will be described in detail in a subsequent publication. In the following, the content and structure of the *LAGOM* program are briefly outlined.

### Individual LAGOM program aspects

The *LAGOM* program will take place over a period of 9 weeks with one session per week. The first and last sessions will last two hours to provide enough time for introduction, group familiarization, and time to review the learned concepts, give a future perspective, and course conclusion. The sessions will last 90 min to enable facilitation during working hours. Meetings will alternate between in-person and online sessions to provide participants more flexibility to take part in the course. The sessions follow the same structure: (1) Introduction with activating movement exercise, observation of a minute of silence for centering after arrival, and reflection (2) psycho-educational part on different topics (see Table 2) with practical exercises and group exchange, (3) a relaxation exercise, (4) session conclusion. Topics have been derived from the needs assessment, complemented with elements from mind–body medicine, such as breathing exercises, various meditation practices, yoga exercises, acupressure, mindful walking, progressive muscle relaxation, imagination exercise, self-reflective exercises, and more. In addition, in-depth material such as self-reflection exercises, guided meditations, or literature resources will be provided and participants will be encouraged to practice 5–15 min daily at home or work. The weekly *LAGOM* sessions will be conducted by mind–body-educated and experienced trainers. A short description of the topics and content that is covered is provided in Table 2.

**Table 2 Tab2:** The LAGOM program: an overview of the session topics, components, and organizational aspects

Session	Topic	Components (examples)	Organizational impulses
1	Introduction to the LAGOM program	• Getting to know each other • Introduction to the “Temple of health” concept • Phases of Behavior change • Goal setting	• Information on already existing occupational health services • Posters and calendars on health topics as visual reminders for hospital wards
2	Stress and stress patterns	• identifying stress patterns • Burnout definition and prevention • Resilience measures/activities/resources	• “Open Ear Policy”: appointment with clinic management to raise concerns and needs
3	Healthy routines in shift work	• Identifying break habits • Learning self-care strategies	• Tips and support for healthy breaks and break room makeovers • Tips to establish daily healthy snacks for wards
4	Cognitive regulation and power of thoughts	• Introduction of the ABC-D concept	• Guidelines for a mental health check-up as part of employee appraisals
5	Managing and developing the “inner team”	• Introduction of the “inner team” concept • identifying needs	• Short massage opportunity at the workplace
6	(Future-)Values in work culture	• Ecosystem clinic, inspired by theory U • Practicing social body scan	• Team coaching/supervision within ward team
7	Communication with others	• Development of empathic, active listening • Introduction of the “compass of needs” idea • Introduction of the stressor identification of 4-ear-model	• Conflict resolution within ward team with external mediation
8	Balance between self-care and care for others	• Protection and mindful use of own resources • Identification of Self-care and self-compassion resources	• Introduction of periodical interdisciplinary “happy hour” lunch breaks
9	“The end of the course is the beginning of…?”—Outlook	• Concept review • Celebrating successes • Conclusion	• Forest therapy sessions as team building for wards of study participants

#### Structural and organizational LAGOM program aspects

In addition, in dialog with the individual hospital wards, structural and organizational aspects will be addressed weekly as well (Table 2). Participants will be able to choose suitable activities according to the different needs and prerequisites of their wards and teams.

### Outcome measures

Data will be collected before (week 0), during (week 1–9) and after the trial (week 10) to assess the acceptability and feasibility of the trial procedures and intervention content. Data will be assessed via SoSci Survey, a web application for online surveys, as well as semi-structured interviews. Data on SoSci is collected and pseudonymized so that an assignment of baseline questionnaires to post-questionnaires but no identification of individuals is possible. Also, the electrophysiological measure analyses planned for the RCT following the feasibility study will be piloted within this study. Table 3 outlines the schedule of enrollment, data collection, and outcome measures.

**Table 3 Tab3:** Feasibility evaluation plan for the *LAGOM* Program

			Study period			
	Measures	Sources	Pre-Intervention	Baseline	*LAGOM*- program	Post-Intervention
				Week 0	Week 1–9	Week 10
Enrollment						
Eligibility screen	Eligibility checklist	Participants	X			
Informed consent and assent		Participants	X			
Data collection						
Sociodemographics	Survey	Participants		X		
Acceptability and feasibility evaluation (*N* = 30)						
Trial procedures						
Recruitment	Study records	Research staff	X			
Attrition	Study records	Research staff			X	X
Completeness of data collection	Study records	Research staff		X		X
Assessment process	Survey	Participants				X
Protocol adherence	Protocol checklist	Trainers, Research staff			X	
Intervention adherence	Study records	Trainers			X	
Intervention content and structure						
Satisfaction	Q4TE	Participants				X
Utility	Q4TE	Participants				X
Knowledge	Q4TE	Participants				X
Application to practice	Q4TE	Participants				X
Organizational results: individual	Q4TE	Participants				X
Organizational results: global	Q4TE	Participants				X
Safety	Study records	Trainers Participants			X	X
Perceived fit and recommendations	Survey	Participants				X
Effectiveness evaluation (exploratory)^a^ (*N* = 30)						
Quality of life						
Burnout symptoms	Questionnaire (MBI)	Participants		X		X
Behavior						
Break habits	Diaries	Participants			X	
Environmental conditions						
Open ear appointment	Email/Phone Call	Participants			X	
Determinants						
Self-efficacy	Questionnaire (BSW-5-REV)	Participants		X		X
Semi-structured interviews (*n* = 3 to 6)						
Perceived barriers	Interviews	Participants				X
Perceived support by supervisor(s)	Interviews	Participants				X
Perceived support from colleagues	Interviews	Participants				X
Perceived benefit on mental health	Interviews	Participants				X
Consolidation	Interviews	Participants				X
Perceived effect on the work environment	Interviews	Participants				X
Recommendations	Interviews	Participants				X
Electrophysiological measures (*n* ≥ 20 with ≥ 10 at each site)						
Accessibility and eligibility of the locality/lab	Survey	Participants		X		
Schedule management	Survey	Participants		X		
Measurement procedure and duration	Survey	Participants		X		
Example HRV estimation based on SDNN and RMSSD	Electrophysiological measures	Participants		X		X

*Q4TE* Questionnaire for Professional Training Evaluation, *MBI* Maslach Burnout Inventory, *BSW-5-Rev* Scale for measuring occupational self-efficacy expectation [Skala zur Messung der beruflichen Selbstwirksamkeitserwartung], *HRV* Heart rate variability, *SDNN* Standard deviation of all NN (heartbeat) intervals, *RMSSD* Square root of the mean squared differences of successive NN intervals

^a^Like the development of the *LAGOM* program, the effect evaluation will be based on Eldredge’s IMA; accordingly, a consideration of the four main components in IMA (quality of life, behavior, environmental conditions, and determinants) is planned

### Demographic data

Sociodemographic variables include age, gender, height, weight, occupation, full-time yes/no, cultural background (optional), and shift work yes/no.

### Acceptability and feasibility evaluation

#### Trial procedures

*Recruitment* is defined as the number (*n*) of participants who were sent a participant information sheet, number who agreed to participate, and number recruited per week. It will be assessed by the research team via study records. *Attrition* is defined as participant dropout over time, recorded by the study team in the study records. Reasons for dropout will be documented for participants who consent to provide a reason but clearly stipulate that giving a reason for study withdrawing is not mandated. *Completeness of data collection* is defined as the recorded number of completed surveys returned to the trial team at each measurement point. It will be assessed by the research team via study records. The *assessment process* will be evaluated via quantitative survey data with regard to comprehensibility, accessibility, and time management. The following statements can be rated on a five-point response scale ranging from 1 = *totally disagree* to 5 = *totally agree*: (1) the survey questions were comprehensible; (2) access to the questionnaires was easy; (3) the time required for completion of the surveys was compatible with my daily work routine; (4) the documentation effort (break behavior, adverse events) was compatible with my daily work routine. *Protocol adherence* is defined as the degree to which the intervention was implemented as prescribed in the protocol, measured through protocol checklists completed by trainers and research staff. *Intervention adherence* is defined as the number of sessions attended, and documented by the trainers.

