#### Intervention content and structure

In order to evaluate intervention acceptability, usefulness, participants´ learning, implementation, and transfer, the Questionnaire for Professional Training Evaluation (Q4TE), a validated training evaluation questionnaire [24] will be used. The questionnaire consists of six subscales (*Satisfaction, Utility, Knowledge, Application to practice, Individual organizational results, and Global organizational results*) with 12 items that can be rated on an 11-point response scale ranging from 0 percent = *completely disagree* (coded as 0) to 100% = *completely agree* (coded as 10). For item 11 (“Overall, it seems to me that the application of the training contents has facilitated the workflow in my company.”) the expression “my company” was changed to “my hospital unit” to more accurately represent the study setting. Previous research has shown that the Q4TE has good discriminant validity and internal consistency (Cronbach’s α = 0.79 to 0.96) [24]. *Safety* is defined as intervention-related adverse events. Safety will be assessed through study records by trainers and participants. *Perceived fit and recommendations* will be further assessed by quantitative survey data and open questions to allow more in-depth information on participants´ experiences with the *LAGOM* program. This will include the following items:The time required to participate in the *LAGOM* program was compatible with my daily work routine (five-point response scale, 1 = *totally disagree* to 5 = *totally agree*).The following course time was most compatible with my daily work routine: (drop-down menu of answers)The group size was appropriate (five-point response scale, 1 = *totally disagree* to 5 = *totally agree*).Would you recommend the *LAGOM* program to other employees? (yes/no and open field for reason)Would you recommend the trainer to other employees? (yes/no and open field for reason)What was particularly helpful about the *LAGOM* program? (open question)What would you recommend changing about the *LAGOM* program? (open question)

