### Exploratory effectiveness evaluation

Since this is a feasibility study without sample size calculation, effectiveness measurements are made purely exploratory to evaluate the feasibility of questionnaires and assessment approaches. Like the development of the *LAGOM* program, the effect evaluation will be based on the IMA, which is why a consideration of the four main components in IMA (quality of life, behavior, environmental conditions, and determinants) is planned [14]. *Quality of Life*: Burnout symptoms will be assessed by the Maslach Burnout Inventory, the German version. The MBI addresses three subscales (Emotional Exhaustion [EE], Depersonalization [DP], and Personal Accomplishment [PA]) with 22 items that can be rated on a scale ranging from 0 = never to 6 = every day with higher scores indicating a higher level of burnout for EE and DP and lower scores indicating a higher level of burnout for PA. Validity and reliability of the MBI have been demonstrated to be good or acceptable (Cronbach´s α > 0.7 for all subscales) [25–27]. *Behavior*: changes in frequency and duration of taking breaks will be assessed daily through a diary, documented by participants throughout the program period. *Environmental conditions*: implementation of open ear appointments (whether they have taken place or not) will be assessed as an indicator of the environmental determinant. Information will be gathered by the research staff from participants via email or phone call. *Determinants*: occupational self-efficacy will be assessed by the BSW-5-Rev (German: Skala zur Messung der beruflichen Selbstwirksamkeitserwartung; scale for measuring work-related self-efficacy) [28]. It consists of 5 items that can be rated on a scale ranging from 1 = *completely disagree* to 4 = *completely agree,* indicating how far the statement applies to oneself or not. Research has shown good construct and criterion validity and acceptable internal consistency (Cronbach’s α = 0.73 for the employee version) [28].

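### One rating covers both the break diary and the adverse-event documentation, and the group-size item gives no direction, so neither answer alone says what to change before the RCT

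*Protocol article*

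**What the plan says.** The section on trial procedures evaluates the assessment process with four statements, each rated from 1 to 5. Table 3 schedules them once, at week 10. The first two read "1) the survey questions were comprehensible; (2) access to the questionnaires was easy", the third reads "3) the time required for completion of the surveys was compatible with my daily work routine", and the fourth reads "4) the documentation effort (break behavior, adverse events) was compatible with my daily work routine".

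The section on exploratory effectiveness explains why these measures are taken at all: "effectiveness measurements are made purely exploratory to evaluate the feasibility of questionnaires and assessment approaches". The measures named there include the Maslach Burnout Inventory (MBI, 22 items), the BSW-5-Rev (5 items) and a daily break diary kept through the programme. Table 3 places the two questionnaires at weeks 0 and 10 and the diary in weeks 1 to 9. Safety is recorded by trainers and participants, and the article does not say how often participants make an entry.

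Among the seven items on perceived fit, in the section on intervention content and structure, one reads "The group size was appropriate (five-point response scale", with anchors running from total disagreement to total agreement.

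**The concern.** The study is meant to refine the procedures and content for a later RCT, so its participant items should point to something that can be changed. Item 4 asks about two tasks that differ in content and purpose. The diary feeds the behavioural outcome and the adverse-event record feeds safety. If the documentation proves too much, the RCT team has to know which of the two to simplify, because the consequences differ. A respondent who found the diary unworkable and the adverse-event form trivial has no way to say so.

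The group-size item has the same practical weakness in another form. Group size can be changed in two directions, and disagreement points to neither.

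Both faults lie in the wording of the questions. They therefore cannot be repaired in an analysis plan once the data are in.

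**Working it through.** The plan has no figure to reproduce here. The sample of 30 is a fixed practical choice, and no hypothesis is tested. The check is a reading of the items, followed by a look at what else could locate a problem.

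**1. The four assessment items**

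| Item | What it refers to | Names a single instrument or task? |
|---|---|---|
| 1, comprehensibility | all survey questions together | no |
| 2, access | all questionnaires together | no |
| 3, time | all surveys together | no |
| 4, documentation effort | break diary and adverse events | no, two tasks in one rating |

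For the two effectiveness questionnaires, one comprehensibility rating covers 22 + 5 = 27 items. The 12-item Q4TE is also in the week-10 survey, but it is an acceptability measure and falls outside the purpose sentence quoted above, so it is not counted.

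**2. What a score on item 4 can mean**

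As an illustration with assumed views, take one participant who would give the diary 2 and the adverse-event record 4, and who settles on the middle: (2 + 4)/2 = 3. Another participant who would give both tasks 3 also answers 3. The data are identical, yet only the first has a problem with the diary.

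The two tasks are unlikely to weigh the same. The diary could have up to 9 × 7 = 63 entries by calendar day, or 9 × 5 = 45 if one assumes five working days a week.

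**3. The seven perceived-fit items**

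- Group size: no direction.
- Time needed for the programme: one global rating.
- The other five can locate a problem: a drop-down for course time, two recommendation items with a field for reasons, and two open questions.

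**4. Other evidence on the diary and the forms**

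- Completeness is defined as the number of completed surveys at each measurement point. Table 3 marks it at weeks 0 and 10, not in weeks 1 to 9 when the diary runs.
- The article lists no open field on the assessment procedures. Its open questions concern the programme.
- None of the listed interview questions mentions questionnaires, diary or adverse-event forms. Survey results may prompt additional ones.
- Interviews reach 3 to 6 people, chosen for range of discipline, unit and site.

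To gauge that last source, suppose k of 30 participants are dissatisfied and m interviewees are drawn at random. Both are assumptions, since the article gives no k and says selection is strategic. The chance of interviewing at least one of them is 1 − C(30−k, m)/C(30, m):

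| k | m = 3 | m = 6 |
|---|---|---|
| 3 | 28% | 50% |
| 6 | 50% | 77% |
| 9 | 67% | 91% |

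The interviews may well miss a problem that troubles a few participants, and will usually reach one that troubles many.

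**The case against.** A reader might infer something stronger: that poor ratings in this study cannot show which instrument or course feature to change. The documents do not support that, for four reasons.

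- **The design is sequential explanatory.** Qualitative work follows the survey to explain it, and the article allows survey results to generate additional interview questions. A low score on item 4 is an obvious trigger. This stands, within limits: few interviewees, not stated to be chosen on their ratings, and no trigger at all if a middling score conceals the problem.
- **The course-format items are mostly sound.** Five of seven are specific, carry a reason field or are open. The open question on what to change goes to all participants and can capture a complaint about group size. This stands, so the point on course format is confined to the missing direction of one item.
- **Other data bear on burden.** The diary is a data source of its own, and gaps in it say something about its burden whatever item 4 shows. Reasons for dropout are also recorded where participants give them. The electrophysiology items rate time, appointment and location separately. This stands, although diary gaps do not speak to the adverse-event record.
- **A survey-level rating can be the right question.** Participants experience the time cost of the whole survey, and a separate time rating for a 5-item scale adds little. The questionnaires are also published scales with reported validity. This stands for item 3 and weakens the case for splitting item 1.

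The criteria for moving to the later trial are in an additional file that is not shown, so it cannot be said that any decision turns on these ratings.

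**Conclusion.** The concern holds in a narrow form and is minor. Item 4 is double-barrelled, and the group-size item lacks direction. In each case the answer alone does not say what to change. Items 1 to 3 refer to the surveys collectively, which is a smaller weakness, and for the time item it is acceptable.

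No estimate is biased, no figure is wrong and no passages contradict each other. What is lost is some of the diagnostic information that a feasibility study is run to obtain. The back-up sources recover part of it.

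The conclusion on items 4 and group size rests only on wording that the article gives in full. The remark that no open field covers the assessment procedures rests on the article's list; the survey as fielded may contain one.

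**What to change.** - Split item 4 into two five-point ratings with the same wording: one for the break diary, one for the adverse-event documentation. Report them separately.
- Replace the agreement scale of the group-size item with three answers: too small, about right, too large.
- Optionally, either ask comprehensibility separately for the MBI and the BSW-5-Rev, or add one open field on the assessment procedures.
- Leave the survey-level time item as it is.

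The cost is one to three extra short items at week 10 and one changed response scale in the existing online survey. The sample, the schedule and the descriptive analysis stay as they are.
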